### 2.5. Interventions

All participants in EG and CG will have same routine obstetric prenatal care following the standard clinical procedures. No intervention will be given to the participants in CG. Participants in EG will perform PGT from the 28th GW to their delivery following the video guidance on mobile app. They will be instructed to download and install the app by research assistants.

The app provides health education and a PGT video. Watching the health education video, participants can learn the pelvic floor anatomy and function and are informed about the negative impact of pregnancy and delivery on PFM. The PGT video includes PFMT and GPR programs designed collaboratively by the urogynecologists and the sports experts. The GPR combines global posture and respiratory training with PFMT to enable participants to exercise PFMT while posturing.

PFMT mainly focuses on voluntary contraction and relaxation of PFM around urethra, vagina and rectum. It provides instruction on coordinating PFM contraction and relaxation by exhalation and inhalation of a breathing circle, respectively, while avoiding the involvement of abdominal muscles. Participants need to contract the PFM first with moderate strength and upholding for 6–8 s, followed by 6–8 s PFM relaxation (the primary PFMT procedure), then repeat primary procedure five times to train the type I muscle fibers. As the second step, participants are asked to do quick maximum PFM contraction and relaxation in 1 s for five times, followed by 10 s of relaxation (the secondary PFMT procedure). The secondary PFMT procedure will be repeated for eight times to train the type II muscle fibers. Both the primary and secondary PFMT procedures need to be repeated for three sets in an exercise circle. Participants in EG need to perform PFMT twice a day following the instruction of the video program. 

The GPR requires the participants to perform respiratory training, PFMT, and global posture simultaneously. It consists of four sets of exercises, each lasting about 30 min and composed of four groups of postures. The postural intensity increases from the first set to the last one. The physiotherapists will instruct the participant to do the proper set of exercises at a specific period according to her gestation weeks. Respiration training during the whole exercise is essential to expand the chest and abdominal cavity that aims to strengthen the relevant muscles. Participants will be guided to exhale deeply while contracting muscles and inhale deeply while relaxing muscles. The program starts with respiratory training in the supine position while performing one set of PFMT, followed by 20 min of aerobic exercise by keeping global postures such as bridge pose, cat pose, child’s pose, and mountain pose, and in-between one set of PFMT is performed. The exercise of GPR will be ended with meditation in the supine position and one set of PFMT will be performed simultaneously. 

The twice-a-week GPR was originally programmed to be performed once following guidance of the app at home and once under face-to-face guidance of the physiotherapists. In consideration that it is not safe to organize face-to-face guidance in training rooms during COVID-19 pandemic and the need to regulate the postures and procedures and collect data to evaluate the compliance of the participants, we modified the protocol to organize video-trainings for EG participants to perform GPR under the living guidance of the physiotherapists on-video via Zoom meetings once a week. Four Zoom meetings will be scheduled for video training in each week, each focusing on one of the four exercise sets. An individual participant will be invited to visit one of the Zoom meeting to practice the exercises appropriate to her GW. Each video-meeting can be divided into several classes according to the number of participants, with each limited to 10 persons, so as to facilitate the physiotherapists to give enough care to each participant and to maximize the effectiveness. The site assistants will notify each participant the Zoom link specially for her in each week in advance, but keep her blind of the other Zoom meeting details to avoid protocol bias. The site assistant will also record the attendance of each participant in terms of the attendance time, the procedural and intensity compliance, and the adverse events, etc. Any participant absent at the scheduled class will be reminded to join the next class on the same exercise set so that she can “catch up” the scheduled one in the following Zoom meeting. The scheduled class will not be cancelled even with only one participant. The role of the physiotherapist is to guide participants in the class to accomplish the full exercise set and to regulate any inappropriate acts. To protect participants’ privacy, no video and audio records are taken and preserved during video-conference, which are fully informed to and consented by the participants.

Any pregnant participant experiencing abnormal symptoms (e.g., abdominal pain, vaginal bleeding, abnormal fetal movement, etc.) will contact the site assistant in each hospital, and the assistant will refer them to the obstetric department as soon as possible, followed by an assessment of whether they should continue the intervention or not. An anticipated adverse event report will be prepared and sent to the principal investigator (PI). 

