Global postural reeducation (GPR) was projected to correct postural misalignments by stretching the muscle chains. As the spine is a continuous boney structure that is closely associated with abdominal and pelvic dynamics, it is commonly recognized that spine restructure through posture reeducation would benefit the functions of the PFMs. Our previous study demonstrated that the spinopelvic skeletal shape had a close relationship with pelvic floor dysfunction [12]. In 1981, Souchard first developed GPR in France, aiming to keep the normal posture to recover muscular strength. Fozzatti et al. [13,14] recruited SUI patients for treatment by the GPR and PFMT, and demonstrated that both GPR and PFMT were effective alternatives for the treatment of SUI, while GPR was significantly more effective. 

To explore a more effective exercise regimen for SUI prevention, we developed a training program through combining PFMT with GPR training (PGT program) under the collaborative efforts from several urogynecologists and sports experts from Peking University.

Patient’s compliance is another important factor for the effectiveness of PFMT. Face-to-face training is time-consuming and needs frequent visits to relevant facilities, which therefore further decreases the adherence to the training program. In addition, it is quite hard to organize face-to-face training programs during the COVID-19 pandemic. For a long time, what has been bothering the urogynecologists is how to achieve intensive supervision and encourage participants to keep high compliance. Popularization of mobile phones makes almost everyone accessible via mobile devices, which enabled women to connect to the world from at home; thus, a PGT video guidance on mobile apps can create potentiality to enhance the adherence and compliance of the patients who can perform PFMT and GPR at home.

Therefore, an app-based video program was developed with the collaboration of software engineers. The video program tends to guide the patients to do regular PFMT and GPR at home or any private room. To make the patients’ compliance evaluable during the COVID-19 pandemic, we integrated a high-intensive online supervision module into the video program. We conduct this multicenter RCT to evaluate the effectiveness and safety of the video program on the prevention of postpartum SUI. 

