### 2.3. Exclusion Criteria

In the first enrollment examination, participants will be excluded if they were confirmed: (1) having serious complications (including uncontrolled brain, lung, heart, liver, kidney, and mental illness; coagulation dysfunction; or obvious cognitive dysfunction) that may be aggravated by the intervention, (2) having SUI or pelvic floor organ prolapse (POP) according to pelvic organ prolapse quantitation (POP-Q) staging, (3) having history of cervical insufficiency, recurrent miscarriage, and induced labor, (4) unable to finish all follow-ups, (5) infecting COVID-19, and/or (6) unable to provide consent in writing (Figure 1). Each participant will be recorded as “drop off from trial” if she suffers from miscarriage, serious complications, or missed all follow-ups. Cesarean will not be the endpoint of the experimental follow-ups.

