### 2.6. Data Collection and Management

Data regarding the clinical examination during the follow-ups will be collected from all participants in both groups. A questionnaire of demographic characteristics including the age, body mass index (BMI), educational status, working type, working posture, toilet type, PFMT history, constipation history, smoking history, number of gestations, number of abortions, family history of SUI, and family history of POP will be collected from the participants with gestation ≤ 16 GWs. The Prolapse/Urinary Incontinence Sexual Questionnaire short form (PISQ-12) [15] will be filled by all participants. Data regarding the MOS, and genital hiatus (gh) and perineal body (pb) measured by pelvic organ prolapse quantitation (POP-Q) of all the participants will be provided by the urogynecologists. Trans-perineal ultrasound using the proprietary software 4D View v 10 (GE Kretz Medizintechnik) will be conducted for all the participants to examine the residual urine, the thickness of pb, detrusor muscle, and levator ani muscle (LAM), and the diameters of the levator hiatus and levator hiatus area. Urinary leakage symptoms, and frequency of PFMT and GPR performance, will be taken from all the enrolled participants respectively at the 28th and 37th GW and at the delivery. Those who have urinary leakage symptoms will fill out the Incontinence Quality of Life (I-QOL) [16] and the International Consultation on Incontinence Questionnaire-urinary incontinence short form (ICIQ-UI SF) [17], and Overactive Bladder Symptom Scores (OABSS) [18] will be assigned to participants who have symptoms of urgency urinary incontinence (UUI). Evaluation of the PFM strength via MOS, stress test, and gh and pb measured by POP-Q will be conducted on all participant in both groups on the 37th GW. The delivery type, the duration of the second labor stage, the perineal laceration classification, the visual analog scale (VAS) score, neonatal Apgar score and the neonatal weight will be recorded during delivery. The visual analog scale (VAS) will be scored at 24 h and 48 h after the delivery to measure the pain degree by scoring 0 to 10. Fetal/neonatal safety will be evaluated with indicators such as the fetal movement, obstetric ultrasound, fetal heart rate, electronic fetal monitoring, neonatal Apgar score, and obstetric examination. 

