### 2.7. The Outcomes

The primary outcome of this study is the occurrence of SUI at the 6th week postpartum, which will be diagnosed based on urinary leakage when abdominal pressure increases or positive stress test. A positive result of the stress test is defined as involuntarily urinary leakage during Valsalva or coughing in the lithotomy position.

The secondary outcomes include: (1) the occurrence of SUI at the 12th month postpartum; (2) the PFM strength at the 6th week and 12th month postpartum, which will be measured with the MOS and pelvic floor electrophysiological test.

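### Safety is a stated aim, but no safety outcome is named and general adverse events are recorded on a schedule only in the exercise group, so comparing those events between arms would not be like for like

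*Protocol article*

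**What the plan says.** **Aim.** The Introduction states: "We conduct this multicenter RCT to evaluate the effectiveness and safety of the video program on the prevention of postpartum SUI".

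**Outcomes.** Section 2.7 gives the primary outcome (SUI at 6 weeks postpartum) and then: "The secondary outcomes include: (1) the occurrence of SUI at the 12th month postpartum", followed by pelvic floor muscle strength at 6 weeks and 12 months. No safety measure is listed. Section 2.9 describes analyses for the primary and secondary outcomes only.

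**Scheduled recording of general adverse events.** Section 2.5 replaces face-to-face sessions with a plan to "organize video-trainings for EG participants to perform GPR under the living guidance of the physiotherapists on-video via Zoom meetings once a week". At these classes the site assistant is to "record the attendance of each participant in terms of the attendance time, the procedural and intensity compliance, and the adverse events". For controls the same section says: "No intervention will be given to the participants in CG".

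**Other sources, not confined to one arm.** Section 2.5 also asks every pregnant participant with abnormal symptoms to contact the site assistant, with an adverse event report going to the principal investigator. It gives both arms the same routine prenatal care. In section 2.6, delivery data are collected without restriction by arm, for example "neonatal Apgar score and the neonatal weight will be recorded during delivery", and fetal/neonatal safety indicators are named. Table 1 schedules fetal/natal conditions before 16 weeks, at 28 and 37 weeks and at delivery, on one schedule for everyone. Table 1 has no row for adverse events.

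**The concern.** The number of adverse events found depends on how often and how directly women are asked. During the training period an exercise-group woman meets, each week, a site assistant whose task includes noting adverse events. A control woman has to recognise a symptom as reportable and make contact herself. Minor and transient maternal symptoms are the most sensitive to this difference, and they include the examples section 2.5 itself gives (abdominal pain, vaginal bleeding).

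If the general adverse-event records are later tabulated by arm, an excess in the exercise group could reflect more frequent asking rather than harm. A real excess could not be told apart from it. Because no safety outcome is named in section 2.7, nothing in the article steers the safety comparison towards the measures that are collected equally. A stated aim is at stake; the primary outcome is not affected.

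**Working it through.** **1. Contact during the training period.** Section 2.5 runs the programme from 28 weeks to delivery, and the Discussion puts its length at 12 weeks. One class a week gives about 12 scheduled occasions for recording adverse events in the exercise group. Both arms share the 28-week, 37-week and delivery visits, but Table 1 schedules no adverse-event item at them. As described, the scheduled occasions for general adverse events are about 12 against 0. Outside the classes, both arms have the symptom-report route and routine care.

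**2. Which measures are affected.**

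| Measure | How collected | Equal between arms? |
|---|---|---|
| General maternal adverse events | Weekly class record (exercise group only), plus self-initiated report (all) | No |
| Fetal/natal conditions | Table 1, one schedule | Yes |
| Apgar score, neonatal weight | At delivery, all | Yes |
| Delivery type, second-stage duration, laceration, pain VAS | At or after delivery, all | Yes |

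**3. The plan's own figure.** The plan gives no adverse-event rate or capture rate. The one input taken from it is the group size. Section 2.8 states 293 per group, and 367 after allowing for 20% dropout. Using unpooled variances:

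n = (1.960 + 1.282)² × (0.257×0.743 + 0.15×0.85) / 0.107² = 10.507 × 0.31845 / 0.011449 = 292.3, so 293; and 293 / 0.80 = 366.25, so 367.

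The figure reproduces and has no bearing on the concern beyond supplying n.

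**4. Illustration, with all rates assumed.** Let the true risk t be equal in both arms, with capture c_E in the exercise group and c_C in controls.

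- Observed risks: p_E = t·c_E and p_C = t·c_C. Apparent risk ratio = c_E / c_C, whatever t is.
- Chance of a false excess in the exercise group at two-sided 0.05: Φ[(p_E − p_C − 1.96·SE0) / SE1], where SE0 = √[2·p̄(1−p̄)/n] and SE1 = √[(p_E(1−p_E) + p_C(1−p_C))/n].

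Worked case: t = 20%, c_E = 90%, c_C = 50%, n = 367.

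- p_E = 0.18, p_C = 0.10, p̄ = 0.14.
- SE0 = 0.02562 and SE1 = 0.02544.
- (0.08 − 1.96×0.02562) / 0.02544 = 1.17, and Φ = 0.879.

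With c_E = 90% and n = 367 throughout:

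| Control capture | Apparent RR | t = 5% | t = 10% | t = 20% |
|---|---|---|---|---|
| 80% | 1.13 | 5.2% | 7.0% | 10.8% |
| 70% | 1.29 | 10.2% | 16.8% | 31.5% |
| 50% | 1.80 | 31.3% | 56.5% | 87.9% |

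With equal capture, the chance in this direction is 2.5% (5% two-sided). If only 293 per arm contribute, the 20% column falls to 26.1% at 70% capture and 79.8% at 50% capture.

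**The case against.** Much can be said for the plan, and most of it narrows the point.

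- **A reader might infer that every between-arm safety comparison is biased.** The documents do not support this. The fetal, neonatal and delivery measures are collected on one schedule, section 2.6 says follow-up examinations cover both groups, and none of this depends on attending a class.
- **A reader might infer that the class record is the only source of adverse events, or that controls have no contact between visits.** Neither holds. The symptom-report route is open to every pregnant participant and leads to a report, and both arms have the same routine care. What remains is that this route is passive, and that its follow-on assessment, about continuing the intervention, has meaning only in the exercise group.
- **No test of adverse events between arms is specified in section 2.9.** Correct. The false-excess probabilities show what such a test would do; they do not describe an analysis that the plan commits to.
- **The article is condensed.** Adverse-event forms, definitions, grading and items such as gestational age at delivery may sit in the full protocol or the SAP, so their absence is not counted here. The secondary outcome list is also worded as what the outcomes include, so it may not be exhaustive. The point rests on what the article does state: a safety aim, an outcome list without safety, and a scheduled recording method that exists in one arm.
- **A reader might infer that harms are discarded**, because section 2.3 records a woman as a drop-off "if she suffers from miscarriage, serious complications, or missed all follow-ups". The section does not say that her events are excluded from safety reporting, and section 2.9 specifies intention to treat.

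**Conclusion.** The concern holds for general maternal adverse events only. Safety is an aim without a named outcome, and scheduled recording of these events is described for the exercise group alone. A between-arm comparison of them would not be like for like, and the likely direction is against the exercise group. That direction assumes that weekly contact captures more events than self-initiated reports and routine care do.

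The size cannot be known from the documents. Under the assumed captures (90% against 50–70%), the apparent risk ratio is 1.29 to 1.80. The chance of a false excess at 367 per arm ranges from about 10% (5% true risk, 70% control capture) to about 88% (20% true risk, 50% control capture). At 80% control capture it is 5% to 11%. These figures illustrate the mechanism and are not estimates for this trial.

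The primary outcome and the equally scheduled safety measures are untouched. It would be wrong to say that the safety question as a whole cannot be answered. The change is still worth making, because it is cheap and protects a stated aim.

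**What to change.** 1. Record adverse events in both arms with the same questions and the same form at the existing shared visits: 28 weeks, 37 weeks, delivery and 6 weeks postpartum. Add the row to Table 1.
2. Base any between-arm comparison of general adverse events on those records only.
3. Report events recorded at classes separately and descriptively, for the exercise group.
4. Name in section 2.7 the safety outcomes already collected in both arms, such as the fetal/neonatal and delivery measures, together with adverse events from the shared form.

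**Cost.** One short form at visits already scheduled and a few lines of text. The comparative analysis will capture events less often than the classes do, so some transient symptoms will be missed, but the method will be the same in both arms. Some difference may remain, since participants are not blinded and the exercise group will have been prompted weekly. Having the form completed by the evaluators who, under section 2.4, are masked would limit any contribution from the person asking.

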### 2.6. Data Collection and Management

Data regarding the clinical examination during the follow-ups will be collected from all participants in both groups. A questionnaire of demographic characteristics including the age, body mass index (BMI), educational status, working type, working posture, toilet type, PFMT history, constipation history, smoking history, number of gestations, number of abortions, family history of SUI, and family history of POP will be collected from the participants with gestation ≤ 16 GWs. The Prolapse/Urinary Incontinence Sexual Questionnaire short form (PISQ-12) [15] will be filled by all participants. Data regarding the MOS, and genital hiatus (gh) and perineal body (pb) measured by pelvic organ prolapse quantitation (POP-Q) of all the participants will be provided by the urogynecologists. Trans-perineal ultrasound using the proprietary software 4D View v 10 (GE Kretz Medizintechnik) will be conducted for all the participants to examine the residual urine, the thickness of pb, detrusor muscle, and levator ani muscle (LAM), and the diameters of the levator hiatus and levator hiatus area. Urinary leakage symptoms, and frequency of PFMT and GPR performance, will be taken from all the enrolled participants respectively at the 28th and 37th GW and at the delivery. Those who have urinary leakage symptoms will fill out the Incontinence Quality of Life (I-QOL) [16] and the International Consultation on Incontinence Questionnaire-urinary incontinence short form (ICIQ-UI SF) [17], and Overactive Bladder Symptom Scores (OABSS) [18] will be assigned to participants who have symptoms of urgency urinary incontinence (UUI). Evaluation of the PFM strength via MOS, stress test, and gh and pb measured by POP-Q will be conducted on all participant in both groups on the 37th GW. The delivery type, the duration of the second labor stage, the perineal laceration classification, the visual analog scale (VAS) score, neonatal Apgar score and the neonatal weight will be recorded during delivery. The visual analog scale (VAS) will be scored at 24 h and 48 h after the delivery to measure the pain degree by scoring 0 to 10. Fetal/neonatal safety will be evaluated with indicators such as the fetal movement, obstetric ultrasound, fetal heart rate, electronic fetal monitoring, neonatal Apgar score, and obstetric examination. 

Four follow-ups will be conducted on all participants respectively on the 6th week and in the 3rd, 6th and 12th month postpartum. To conduct the multiple physical valuations in a time-saving way, it is proposed to check the participant in the following sequence: first, check the stress test, POP-Q, MOS when the bladder is half-full; second, conduct the pelvic floor ultrasound examination and the pelvic floor electrophysiological test (Electron-IC Concept Lignon Innovation Co., Montpellier, France) with the emptied bladder; and last, fill the PISQ-12. The pelvic floor electrophysiological indicators mainly include the vaginal resting pressure (cmH2O), the vaginal maximum contraction pressure (cmH2O) and PFM fatigue (%). I-QOL, ICIQ-UI SF, and OABSS will be provided to participants who show symptoms of urinary leakage or UUI as appropriate (Table 1).

Gynecologic examination, pelvic floor ultrasound, pelvic electromyography, and fetal safety will be evaluated respectively by the urogynecologists, ultrasound professors, electromyography nurses, and obstetric professors in each hospital, who will be trained in the Peking University People’s Hospital before the launch of the study. A program that is preset into the video will record times for the full-playing of the video and automatically transfer the data into the database as the training frequency for each participant. The site assistants will confirm the training frequency of each participant in EG every week by checking the records from the online-guided software, exercise diary, and the video-training. Accomplishment of PFMT will be identified for each participant should she accomplish more than 80% of the training programs prescribed for every week. 

Data input devices will be provided to the hospitals to be involved in the research. Paper files will be prepared and kept for each participant to record all data to be collected in the full study stage. Exercise diaries from participants in EG will be used to evaluate their PFMT frequency and training intensity. The database will be protected from access by a password, and the final dataset will only be accessible to the PI, and, under authorization of the PI, to the study coordinator. Desensitized data are available for research purpose only per the permission of the PI. 

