### 2.4. Randomization and Allocation Concealment

A randomization list will be created by a statistician from Peking University for each center before the start of the research using SAS 9.4 (SAS Institute, Cary, NC, USA). The numbers of participants in EG and CG are balanced, with a 1:1 ratio, and put into blocks of four. A unique study ID will be given to each participant. 

The randomization result for EG and CG are sealed in the ID-matching envelopes. The grouping details will be concealed to the investigators who will account for group allocation, recruitment, informed consent, and data collection. Eligible women are informed of grouping allocation via opening the sealed envelope after signing the informed consent. It is not feasible to blind to participants, urogynecologists and physiotherapists engaging in the intervention. However, all the investigators to perform patient evaluation and data analysis will be masked.

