## Figures and Tables

**Figure 1 ijerph-18-12929-f001:**
[figure not shown]
Study flow.

**Table 1 ijerph-18-12929-t001:** Baseline screening, assessment, and follow-up schedule.

	At Pregnancy				At Postpartum			
	<16th Week	28th Week	37th Week	Delivery	6th Week	3rd Month	6th Month	12th Month
Follow-up schedule (week)	0	± 1	± 1	± 1	± 1	±2	± 2	± 2
Informed consent	•							
Demographic data collection	•							
Urinary leakage symptoms	•	•	•	•	•	•	•	•
Training frequency	•	•	•	•	•	•	•	•
Pb and gh	•		•					
Stress test	•		•		•	•	•	•
POP-Q staging					•	•	•	•
The modified Oxford Scale	•		•		•	•	•	•
The duration of the second labor stage				•				
The perineal laceration classification				•				
VAS				•				
Fetal/natal conditions	•	•	•	•				
Pelvic floor ultrasound	•				•	•	•	•
Pelvic floor electrophysiological test					•	•	•	•
PISQ-12	•				•	•	•	•
ICIQ-UI SF		▲	▲		▲	▲	▲	▲
OABSS		▲	▲		▲	▲	▲	▲
I-QOL		▲	▲		▲	▲	▲	▲

•: Indicates mandatory items; ▲: Investigator will decide whether to perform the test according to clinical signs or clinical evaluation. Pb: perineal body; gh: genital hiatus; POP-Q: pelvic organ prolapse quantitation; VAS: visual analog scale; PISQ-12: Prolapse/Urinary Incontinence Sexual Questionnaire short form; ICIQ-UI SF: the International Consultation on Incontinence Questionnaire-urinary incontinence short form; OABSS: Overactive Bladder Symptom Scores; I-QOL: the Incontinence Quality of Life.

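### A leakage report from a woman who knows her arm is enough for a primary event, which examiner masking cannot protect, and training frequency is recorded at outcome visits with nothing to keep it from the examiner

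*Protocol article*

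**What the plan says.** **Masking.** Section 2.4 says: "It is not feasible to blind to participants, urogynecologists and physiotherapists engaging in the intervention". It then says that "all the investigators to perform patient evaluation and data analysis will be masked".

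**Primary outcome.** Section 2.7 defines SUI at 6 weeks postpartum as a condition "which will be diagnosed based on urinary leakage when abdominal pressure increases or positive stress test". The Abstract instead names symptomatic SUI *and* a positive stress test.

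**Training data.** For weeks 28 and 37 of pregnancy and for delivery, Section 2.6 says: "Urinary leakage symptoms, and frequency of PFMT and GPR performance, will be taken from all the enrolled participants". The stress test and modified Oxford Scale (MOS) are done at 37 weeks too. Table 1 has a row "Training frequency", marked mandatory at all eight time points. At 6 weeks postpartum it stands in the same column as leakage symptoms, stress test and MOS.

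**Who does what.** In Section 2.6, urogynecologists at each hospital do the gynecologic examination. The app sends full video plays to the database as training frequency, and site assistants confirm the exercise group's (EG) frequency weekly. A paper file per woman holds all study data. At postpartum visits the proposed order is stress test, POP-Q and MOS first, then ultrasound and electrophysiology, then PISQ-12.

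**Analysis.** Section 2.9 compares 6-week SUI between arms by chi-square or Fisher's exact test. The sensitivity analyses it names concern missing values.

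**The concern.** There are two weaknesses, of different strength.

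1. **Self-report.** The stated safeguard against assessment bias is a masked examiner. Under the *or* rule, the examiner's reading decides the outcome only for a woman who reports no leakage. EG women receive education on the pelvic floor and weekly live coaching, while controls receive no intervention. The arms may therefore report leakage differently for reasons unrelated to continence. Part of an observed difference in the primary outcome, or part of its absence, could then be a reporting effect. No analysis named in Section 2.9 separates it out, and the limitations in the Discussion do not mention it.

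2. **Possible unmasking of the examiner.** GPR is delivered through the trial's app and the EG video classes, so an antenatal GPR frequency comes close to naming the arm. If the examiner sees it before grading the stress test and MOS, the masked component is weakened as well.

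**Working it through.** **Step 1: which component can masking protect?** Four combinations of report and test are possible.

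| Reported leakage | Stress test | Section 2.7 (*or*) | Abstract (*and*) |
|---|---|---|---|
| yes | positive | event | event |
| yes | negative | event | no event |
| no | positive | event | no event |
| no | negative | no event | no event |

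Under Section 2.7, a report makes an event in the second row without any support from the test. Under the Abstract it cannot, although a woman who does not report leakage can still remove an event (third row). Unmasked report matters under both rules, but only the *or* rule makes it sufficient.

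**Step 2: does the text tie training frequency to the examiner?** The sentence in Section 2.6 covers 28 and 37 weeks and delivery only. The link to 6 weeks comes from the Table 1 row, which does not name GPR. No sentence says that the examiner takes or sees the item, and none says that it is withheld. The postpartum order in Section 2.6 places neither the symptom interview nor training frequency, and it does not cover 37 weeks.

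**Step 3: the plan's own sample size.** Inputs from Section 2.8: 25.7% v 15%, two-sided 0.05, 90% power. With the unpooled normal formula:

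n = (1.960 + 1.282)² × (0.257×0.743 + 0.15×0.85) / 0.107² = 292.3, so 293 per group.

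Dropout: 293/0.80 = 366.25, so 367 per group and 734 in total. Both figures reproduce, and this point does not change them.

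**Step 4: illustration of a reporting difference.** Assumptions that are not in the documents: no true effect, and a shift of d in favour of EG. With n = 293 per arm, the probability of significance in favour of EG is

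Φ[(d − 1.96·SE₀)/SE₁], where SE₀ = √(2p̄(1−p̄)/n) and SE₁ = √((p₁(1−p₁)+p₂(1−p₂))/n).

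| Base rate | Shift | SE₀ | SE₁ | z | Probability |
|---|---|---|---|---|---|
| 25.7% (Section 2.8) | 3 points | 0.0354 | 0.0354 | −1.11 | 13% |
| 25.7% | 5 points | 0.0349 | 0.0348 | −0.53 | 30% |
| 20% (assumed) | 3 points | 0.0321 | 0.0321 | −1.03 | 15% |
| 20% | 5 points | 0.0314 | 0.0313 | −0.37 | 36% |

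Without bias, this one-direction probability would be 2.5% (5% for both directions).

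**Step 5: what such a shift requires.** Under the *or* rule, under-reporting changes the outcome only in stress-test-negative women. At 25.7%, a 3-point shift needs 3/25.7 = 12% of EG events to rest on symptoms alone and go unreported; a 5-point shift needs 5/25.7 = 19%. The documents give no share of symptom-only events. Let s be that share and u the fraction of those events that EG women do not report, so that the EG rate is 0.257(1 − s·u). The two-sided rejection probability is then 11% at s = 0.5, u = 0.2. It runs from 5.4% (s = 0.25, u = 0.1) to 62% (s = 1, u = 0.3).

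**The case against.** A reader might infer that collecting training frequency reveals the arm to the person who then grades the stress test. The documents do not support that. They give the task to the app and the site assistants, and they already propose the stress test and MOS first among the postpartum examinations. The intervention runs only until delivery, so current frequency at 6 weeks need not identify the arm, and the Discussion accepts that controls may do PFMT on their own. Section 2.4 lists urogynecologists engaged in the intervention as unmasked and Section 2.6 uses urogynecologists as examiners, but these may be different people. This limb therefore stands only as an open risk, clearest at 37 weeks.

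It can also be said that SUI is in large part a symptom, that participants cannot be masked in an exercise trial, and that the protocol says so. That is fair, and it is why the remedy leaves the primary outcome in place. A supportive analysis could also be placed in an analysis plan that is not shown. The point here is narrower: a stated endpoint rule limits what a stated masking safeguard can do.

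Finally, the direction of bias is not known. Education could make EG women notice and report more leakage, which would work against the intervention.

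**Conclusion.** The point holds in two parts. First, if Section 2.7 governs, unmasked self-report is sufficient for a primary event, and examiner masking cannot protect that component. This follows from the text, subject to the conflict with the Abstract, which has to be settled. Second, training frequency is collected at the visits where masked examinations are done, with no stated separation. That is a risk left open, not a demonstrated break of masking.

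The size is illustrative only: about 13% or 30% significant results in favour of EG at the protocol's 25.7% for an assumed 3- or 5-point shift, and 15% or 36% at an assumed 20%. These figures show that a modest reporting difference could matter at this sample size. They do not show that one will occur, or in which direction. The sample size calculation is unaffected.

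**What to change.** 1. State one definition of the primary outcome, and use it in both the Abstract and Section 2.7.
2. Prespecify the 6-week stress test alone, read by the masked examiner, as the key supportive analysis of the primary outcome.
3. Extend the examination order in Section 2.6 to every outcome visit, including 37 weeks. Complete symptoms, stress test and MOS first; only then is training frequency taken by the site assistant or from the app record. State that the examiner does not see it beforehand.

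**Cost.** Table 1 already makes the stress test mandatory at 6 weeks, so no new data, staff or participants are needed. The added analysis will have fewer events than the *or* outcome and so lower power; it should be read for consistency of direction and size, not as a second test of the primary hypothesis. Reordering the visit changes procedure only.
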